### Procedure

Procedures for recruitment, eligibility determination, and enrollment are presented in Textbox 1

Textbox 1.Procedures for recruitment, eligibility determination, and enrollment.Potential candidates are recruited through a dedicated internet home page and community-based institutions that support people with mental illnesses.People interested in participating in the study should email [name].[name] sends a study description to potential candidates by email or by post.Potential candidates read the study description, and if they have questions about the study, they submit their inquiries via email or phone. If they understand the study description and agree to participate, they send a written consent form to [name] by email or post.Once the consent forms are received, [name] assesses participants’ eligibility via email. The author confirms that potential candidates meet the inclusion criteria, such as providing support to people with mental illness in the community, holding relevant qualifications, and being at least 18 years old, and also confirms that they do not meet the exclusion criteria, such as an inability to use Zoom conferencing or online surveys and an inability to participate in group discussions in Japanese. Those who meet the criteria are enrolled as study participants.[name] emails those who have confirmed their eligibility. Study participants complete the baseline questionnaire (T1) using REDCap (Research Electronic Data Capture; Vanderbilt University).[name] uses REDCap to randomly allocate the study participants who have completed the baseline questionnaires (T1).[name] informs participants by email about their allocated group and the upcoming schedule.For intervention groups, the textbook and “Mana Book” (level 4) are mailed to participants 2 weeks before the start of the program, and they are asked to read them before attending.Participants in the intervention group participate in the program within 2 months of allocation and complete questionnaires immediately after the program (T2) and 1 month later (T3), whereas participants in the control group complete questionnaires 1 month (T2) and 2 months (T3) after allocation.After completing the final questionnaire (T3), participants in the control group may voluntarily attend the program.

### Assessment Plan

#### Demographic Variables

Demographic data collected for study participants include age, ethnicity, assigned sex at birth, occupation, workplace, provision of individual support, management position, years of practice, years supporting individuals with mental illness, experience in providing sexuality-related support, experience receiving sexuality education, and motivation for participation.

#### Outcome Variables

##### Confidence in Providing Sexuality-Related Support

The primary outcome is confidence in providing sexuality-related support, measured using the self-assessment scale of the lack of quality of sexuality education [51]. This scale was originally developed to self-assess the quality of sexuality education that parents provide to their children. In this study, we replace “child” with “client.” It is a 6-item, 1-factor scale that has been examined for validity and reliability [51]. The items are: “I don’t know how to talk to the client about sexuality,” “I don’t know what and how much I should teach the client about sexuality,” “I can’t find a way to give them knowledge about sexuality,” “I feel embarrassed to talk to the client about sexuality,” “My knowledge of sexuality is insufficient to provide sexuality education,” and “I don’t know what the client knows about sexuality.” Responses to the 5-point Likert scale range from 1 (“Not at all applicable”) to 5 (“Very applicable”). Total scores range from 6 to 30. Lower scores indicate higher confidence in providing sexuality-related support.

##### Attitudes Toward Sexuality

Attitudes toward sexuality are a secondary outcome measured by the Attitudes Toward Sexuality Scale [52]. A liberal attitude toward sexuality within the profession is a prerequisite for recognizing the need for care regarding sexuality and for maintaining the flexibility to respond to clients’ diverse human values and ways of life [53]. The scale comprises 37 items and 5 subscales measuring attitudes toward sexuality, and has been examined for validity and reliability [52]. The subscales are: “Attitudes Toward Sexual Minorities” (12 items), “Attitudes Toward Sexual Reproductive Bias” (8 items), “Attitudes Toward Sexual Desire and Heterosexuality Among Older Adults and Women” (9 items), “Attitudes Toward Sexual Violence” (4 items), and “Repressive Attitudes Toward Female Sexuality” (4 items). Each item is rated on a 5-point Likert scale, with responses ranging from 1 (“Very much agree”) to 5 (“Very much disagree”). No overall score is obtained; instead, the sum of the scores for each of the 5 subscales is calculated. The higher the score, the more liberal the attitude toward sexuality; conversely, the lower the score, the more conservative the attitude.

### Knowledge of Sexuality Education

Knowledge of sexuality education is a secondary outcome. The items test knowledge about the content of the textbook “Mana Book” and include items such as “Outing is talking about things that pertain to your privacy that you have not shared before” [15]. The test consists of 30 items with “Correct,” “Wrong,” and “Don’t know” options. Scores are totaled, with 1 point awarded for each correct answer. Total scores range from 0 to 30.

### Knowledge of Preconception Care for People With Mental Illness

Knowledge regarding preconception care for people with mental illness is a secondary outcome. The items are based on perinatal clinical practice guidelines for women with mental illness published by academic societies [54]. The 5 items, such as “It is desirable for mental illness to be stable for at least 3 months before becoming pregnant” and “Most psychotropic medications are compatible with breastfeeding,” have been used in a survey [36]. Responses are “I knew” and “I didn’t know.” The scores (1 point for “I knew”) are totaled. Scores range from 0 to 5.

### Process Assessment

The process assessment is conducted only on the intervention group. It includes questions about satisfaction (multiple choice and free text), whether the program would be useful for future support (multiple choice and free text), whether they would recommend the program to other practitioners (multiple choice and free text), and what changes occurred (free text). How the support was reflected during the 1-month follow-up period will be shown through an analysis of the qualitative data obtained from “What changes occurred (free text).”

Demographic variables are collected during the baseline assessment (T1). Outcome variables are collected during the baseline assessment (T1), assessment 1 (T2), and assessment 2 (T3). A process assessment is conducted at T3 only for the intervention group. Table 2 shows the contents of the questionnaire.

**Table 2. T2:** Content of the questionnaires.

Assessment	Demographic variables	Outcomes
T1 (baseline assessment)	✓	✓
T2 (following assessment 1)		✓
T3 (following assessment 2)		✓

### Study Hypotheses

The hypotheses of this study are (1) the intervention group will have higher confidence in providing sexuality-related support at T3 than the control group (hypothesis 1), (2) changes in confidence in providing sexuality-related support scores from T1 to T2 and T3 will be greater in the intervention group than in the control group (hypothesis 2), (3) scores on the Attitudes Toward Sexuality Scale at T3 will be higher in the intervention group than in the control group (hypothesis 3), (4) changes in the scores on the Attitudes Toward Sexuality Scale from T1 to T2 and T3 will be greater in the intervention group than in the control group (hypothesis 4), (5) scores for knowledge of sexuality education at T2 and T3 will be higher in the intervention group than in the control group (hypothesis 5), and (6) scores for knowledge regarding preconception care for people with mental illness at T2 and T3 will be higher in the intervention group than in the control group (hypothesis 6).

### Analysis Plan

#### Statistical Analysis

The primary analysis will be conducted on the full analysis set (FAS), with supplementary analyses performed using the per-protocol set. The FAS will include all enrolled participants except those who meet the following exclusion criteria: (1) no response at T1 and (2) not randomized. The per-protocol set will consist of participants in the FAS except those who meet the following exclusion criteria: (1) no response at T2 and/or T3, (2) assignment to the intervention group but attendance at fewer than half of the program sessions, and (3) withdrawal from the study during the intervention period.

Baseline data for continuous variables will be summarized as mean and SD or as median and IQR, whereas categorical variables will be summarized as frequencies and percentages.

For the main hypothesis 1, a Student 2-tailed *t* test will be conducted, and a 95% CI will be calculated. An analysis of covariance will be conducted with assigned sex at birth and baseline values included as covariates, and the difference in least squares means, along with its 95% CI, will be estimated.

For hypotheses 2 and 4, a mixed-effects model for repeated measures (MMRM) will be conducted with group, time points (T1, T2, and T3), and the interaction between group and time points as fixed effects, and participants as a random effect. The variance-covariance structure of the error terms in the MMRM will be tested in the following order: unstructured, compound symmetry, and auto-regression. The estimation results based on the first successful convergence of the specified structure will be adopted. MMRM estimation will be conducted using the restricted maximum likelihood method.

For hypothesis 3, the same analysis as that for the main hypothesis will be conducted.

For hypotheses 5 and 6, the Wilcoxon rank-sum test will be conducted at time points T2 and T3. Since these are secondary end points, no adjustments for multiplicity will be made.

All statistical analyses will be conducted using IBM SPSS (Statistical Package for the Social Sciences) Statistics (version 23).

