### Random Allocation and Blinding

KN prepared an allocation list stratified by assigned sex at birth (female or male). In Japan, policy guidance has generally favored assigning practitioners of the same sex for care that service users may perceive as sensitive or embarrassing, partly to protect the rights and dignity of people with disabilities [49]. Practitioner sex may therefore influence the effectiveness of the program, as providing sexuality-related support to same-sex versus opposite-sex clients may affect the content and type of counseling offered. In addition, understanding of sexual diversity remains limited in some settings in Japan; even health care practitioners may encounter discrimination related to sexual minority status [36], and some individuals may be reluctant to disclose their gender identity even when distressed [50]. These sociocultural factors influenced the study design and informed the decision to avoid stratification based on gender identity. Randomization was therefore stratified by sex assigned at birth in order to reduce the privacy burden associated with collecting sensitive personal information.

The allocation is performed using REDCap (Research Electronic Data Capture; Vanderbilt University), a widely used web application for building and managing online surveys and databases. KN prepared the allocation list before enrollment began. REDCap locks the randomization model to ensure that it is not modified once a study becomes active. After [name] confirms that participants have responded to the online survey (T1), [name] enters the assigned sex at birth data into REDCap, and random allocation is performed automatically. [name] communicates the allocation results displayed in REDCap to participants by email. Group assignment is unknown to researchers other than [name]. [name] is the sole individual with access to the test dataset, which is managed through REDCap. [name] is responsible for extracting group information from the final dataset and subsequently providing the dataset to [name] for statistical analysis.

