### Sample Size

We plan to recruit 76 participants. A previous study [51] conducted a similar intervention; in that study, the average scale score of the primary outcome variable before the training was 23.39, and the average scores 1 week and 3 months later were both 18.56. In our study, we assume that the intervention group’s average score 1 month after the intervention will be 18.56, compared with 23.39 for the control group. Furthermore, the previous study [51] that examined the validity of the scale reported an average of 19.5 (SD 5.5). In our study, taking into account the intervention and the characteristics of the participants, the SD is assumed to be 6.5.

Under the above assumptions, if a 2-tailed *t* test is used with an α error of 5% on both sides and a power of 80%, the required sample size is 60 (n=30 for each group). After considering a dropout rate of 20%, the required sample size is 76. The study’s intervention is administered on a group-by-group basis; however, given the nature of the intervention, the expected small group effect allows for a sample size calculation method that presumes independence.

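### The main hypothesis is given both an unadjusted t test and an ANCOVA, and the plan does not say which one decides

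*Protocol article*

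**What the plan says.** Hypothesis 1 (Study Hypotheses) is one comparison at one time: confidence at T3, intervention against control. The Statistical Analysis section gives it two analyses in consecutive sentences:

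- The unadjusted test comes first: "For the main hypothesis 1, a Student 2-tailed *t* test will be conducted, and a 95% CI will be calculated".
- The adjusted analysis comes second and reports a least squares mean difference with an interval of its own: "An analysis of covariance will be conducted with assigned sex at birth and baseline values included as covariates".

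Neither is labelled primary, supportive or sensitivity. Where that section speaks of a primary analysis, it distinguishes the full analysis set from the per-protocol set, not one test from another. The waiver of multiplicity adjustment is justified by the end points being secondary, so it does not cover hypothesis 1. Hypothesis 3 takes over the same pair of analyses.

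The Sample Size section works from the t test: "if a 2-tailed *t* test is used with an α error of 5% on both sides and a power of 80" percent. The Random Allocation and Blinding section states: "Randomization was therefore stratified by sex assigned at birth". The reason given there is that the practitioner's sex may affect how well the program works.

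**The concern.** A trial with one main hypothesis needs one result that settles it. Here two standard analyses of the same contrast are planned without a ranking, and they can fall on opposite sides of 5%. What is at stake depends on how the gap is filled:

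- **The t test decides.** The decisive test then ignores the baseline score on the same scale, which every randomised participant has, and the factor used to stratify. Precision that costs nothing is not used.
- **Either test may be claimed.** The main hypothesis then has two chances at 5%, and the error rate exceeds 5%.

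In both cases, if the verdicts differ, nothing written in advance tells the reader which one the conclusion follows.

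**Working it through.** **Inputs from the Sample Size section.** Means: "the intervention group’s average score 1 month after the intervention will be 18.56, compared with 23.39 for the control group", a difference of 23.39 − 18.56 = 4.83. Spread: "the SD is assumed to be 6.5". Standardised difference: 4.83 / 6.5 = 0.743. Two-sided alpha 0.05, power 80%. Size: "the required sample size is 60 (n=30 for each group"; then "After considering a dropout rate of 20%, the required sample size is 76".

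**Assumed input.** The correlation r between baseline and T3 scores is not in the document. I use 0.3, 0.5 and 0.7.

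**Step 1: reproduce the plan's figure.** The noncentrality is 4.83 / (6.5 × √(2/30)) = 2.878 on 58 df. Exact power is 80.8% at 30 per group and 79.4% at 29, so 30 per group (60 in total) is right. Dropout: 30 / (1 − 0.20) = 37.5, rounded up to 38 per group, which is 76. The stated sample size stands.

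**Step 2: power of the planned ANCOVA at 30 per arm.** The residual SD is 6.5 × √(1 − r²), and two further df are spent on the covariates (56 df). Sex is credited with no explanatory value.

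| r | Residual SD | Noncentrality | ANCOVA power (formula) | t-test power |
|---|---|---|---|---|
| 0.3 | 6.20 | 3.02 | 84% | 81% |
| 0.5 | 5.63 | 3.32 | 90% | 81% |
| 0.7 | 4.64 | 4.03 | 98% | 81% |

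Simulation, which also carries chance imbalance in the covariates, gives about 83%, 89-90% and 97-98%. Evaluable numbers per arm for 80% power with ANCOVA would be 27, 23 and 16, against 30 for the t test.

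**Step 3: error rate if either test may be claimed.** Trials were simulated with no treatment effect, 30 per arm, with both tests run on the same data. Each test alone holds 5%. At least one is significant in about 6.5% (r = 0.3), 7.3-7.5% (r = 0.5) and 8.1-8.5% (r = 0.7) of trials. Two independent tests would give 1 − 0.95² = 9.75%. The two tests here share the same outcomes and are correlated, so the figure stays below that.

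**Step 4: how often the verdicts differ.** At the planned effect, one test is significant and the other is not in about 7%, 12% and 17-18% of simulated trials. At r = 0.5 that is roughly one trial in eight.

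**The case against.** The case for the plan is substantial.

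- **The text leans to the t test.** It comes first, it is tied to the main hypothesis, and it is the basis of the sample size. The ANCOVA sentence is worded as estimation. A fair reader may take the t test as the inference and the ANCOVA as an adjusted estimate. This stands as a hint, but the article does not say it.
- **An unadjusted t test in a randomised trial is valid.** It holds 5%, its standard error already allows for chance baseline imbalance, and it meets the stated power. This stands in full. The point is about efficiency and clarity, not validity.
- **The figures depend on an undocumented r and on 30 per arm, which is the number left after the assumed dropout.** This also stands. The Results section reports no dropouts by 12 March 2026. With all 76 evaluable (38 per arm), t-test power is 89% and ANCOVA power 92%, 96% and 99% for the three correlations, so the gap narrows.
- **A fuller plan may rank the analyses.** That is possible. But the article itself prints both analyses of its main hypothesis, and which one settles it is a protocol-level choice.

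A reader might infer that the plan both loses power and inflates alpha. It cannot do both. Power is lost only if the t test alone decides, and alpha rises only if either test counts. Under an either-test rule, power is at least that of the ANCOVA. Nor does any sentence say that success on either test will count; that is one way to fill a gap, not a stated rule.

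**Conclusion.** The point holds as an unranked pair of analyses for the main hypothesis. It does not show an invalid test, an underpowered trial or a wrong sample size.

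On the more natural reading (the t test decides), the cost is forgone power: about 2-3 percentage points at r = 0.3, 9 at r = 0.5 and 17 at r = 0.7, with 30 per arm and the planned effect. On the other reading (either test may be claimed), the cost is 1.5 to 3.5 percentage points of extra type I error over the same range. On any reading, discordant verdicts are common enough that the rule should be written down first. The sizes rest on the assumed r of 0.3 to 0.7, on the plan's own difference and SD, and on independent participants, as the Sample Size section supposes.

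Severity: should-fix. A valid t test that meets its stated power does not justify a stronger grade.

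**What to change.** Before outcome data are analysed by group, add one sentence to the Statistical Analysis section. It should say that the single decisive analysis of hypothesis 1 is the planned ANCOVA difference at T3, adjusted for baseline score and sex assigned at birth, with its 95% CI, and that the t test is supportive. Use the same ranking for hypothesis 3. Keep N = 76; sized on the t test, it is conservative for the ANCOVA.

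The cost is one sentence and 2 df. No new data are needed, and the ANCOVA is already planned. At 12 March 2026, 46 participants had completed the final assessment and no analysis had been done, so the choice can still be made without sight of results. The Ethical Considerations section already provides for board review of protocol changes.

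### The MMRM for hypotheses 2 and 4 gives each arm its own T1 mean, so its change contrasts are valid but less precise than a baseline-adjusted analysis, chiefly at T2

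*Protocol article*

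**What the plan says.** All locations are in the protocol article.

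- **Hypotheses 2 and 4 (Statistical Analysis).** The MMRM "will be conducted with group, time points (T1, T2, and T3), and the interaction between group and time points as fixed effects". Each participant also has a random effect. For the error covariance, the structure "will be tested in the following order: unstructured, compound symmetry, and auto-regression". T1 is thus one of three response levels. There is no baseline covariate, no equal-baseline constraint and no sex term.
- **Hypotheses 1 and 3 (Statistical Analysis).** "For the main hypothesis 1, a Student 2-tailed *t* test will be conducted, and a 95% CI will be calculated". In addition, "An analysis of covariance will be conducted with assigned sex at birth and baseline values included as covariates". For attitudes the plan is carried over: "For hypothesis 3, the same analysis as that for the main hypothesis will be conducted".
- **Targets (Study Hypotheses).** Hypothesis 2 is that "changes in confidence in providing sexuality-related support scores from T1 to T2 and T3 will be greater in the intervention group"; hypothesis 4 is the same for attitudes. Hypotheses 1 and 3 concern T3 only.
- **Timing and stratification.** Study Design, Random Allocation and Blinding, and the Procedure textbox all place the T1 questionnaire before allocation. "Randomization was therefore stratified by sex assigned at birth".

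**The concern.** Because T1 precedes allocation, any T1 difference between the arms is chance. A model with a free group effect at T1 treats that chance difference as something to estimate and subtracts all of it from the follow-up difference. Baseline adjustment removes only the part that predicts follow-up, and so has the smaller variance.

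The stake is precision, and it differs by time point. At T3 the plan already has a baseline- and sex-adjusted estimate for confidence and for each attitude subscale, through the ANCOVA for hypotheses 1 and 3. At T2 the MMRM is the only planned analysis of those six scores, so no baseline-adjusted T2 estimate will exist.

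A smaller matter is presentation. At T3 the hypothesis 1 ANCOVA and the hypothesis 2 contrast target the same effect under randomisation, but they will generally give different numbers. The article does not say that they address one quantity.

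**Working it through.** **Inputs.** From Sample Size: control mean 23.39, intervention mean 18.56, so the difference is 4.83; SD 6.5; two-sided 5% level; 80% power; 30 per group; 76 after 20% dropout. The T1-to-follow-up correlation r is not in the documents, so it is assumed and a range is shown.

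**Reproducing the plan's figure.** The normal approximation gives 2 × (1.960 + 0.842)² × 6.5² / 4.83² = 28.4, or 29 per arm. Noncentral t power is 79.4% at 29 and 80.8% at 30, so 30 per arm is right for the t test. For dropout, 30/0.8 = 37.5, rounded up to 38 per arm, or 76. The sample size stands.

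**What the MMRM contrast is.** The model has a free mean for each arm at each time. With complete data its fitted means are the observed cell means, so the T1-to-T3 contrast is the raw difference in mean change. On one simulated data set (30 per arm) the raw differences were −5.962 at T2 and −4.673 at T3. The fitted contrasts were identical under unstructured, compound symmetry and autoregressive covariance.

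**Variance.** With equal SD σ at both times and n per arm:

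- change contrast: 2σ²(1−r) × 2/n
- baseline-adjusted contrast: σ²(1−r²) × 2/n
- ratio: 2(1−r)/(1−r²) = 2/(1+r)

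With unequal SDs s₁ (T1) and s₂ (follow-up), the per-person excess is s₁² + s₂² − 2r·s₁s₂ − s₂²(1−r²) = (s₁ − r·s₂)². It is never negative, and is zero only if the slope of follow-up on baseline is 1.

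**Numbers** (σ = 6.5, n = 30 per arm, difference 4.83):

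| assumed r | SE, change | SE, adjusted | variance ratio | power, change | power, adjusted |
|---|---|---|---|---|---|
| 0.3 | 1.986 | 1.601 | 1.54 | 66.7% | 84.3% |
| 0.5 | 1.678 | 1.453 | 1.33 | 80.8% | 90.4% |
| 0.7 | 1.300 | 1.199 | 1.18 | 95.5% | 97.7% |
| 0.8 | 1.061 | 1.007 | 1.11 | 99.4% | 99.7% |

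For example, at r = 0.5 the change SE is 6.5 × √(2 × 0.5 × 2/30) = 1.678 and the adjusted SE is 6.5 × √(0.75 × 2/30) = 1.453. A simulation of 4,000 trials gave SEs of 1.995 against 1.653 (r = 0.3), 1.667 against 1.461 (0.5) and 1.307 against 1.210 (0.7). The power columns use the T3 assumption for confidence. The documents give no effect or SD for T2 or for the attitude subscales, but the variance ratio applies to them with their own r.

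**Effect of the constraint.** Forcing equal T1 means, under compound symmetry with r = 0.5, lowers the T3 contrast SE from 1.678 to 1.453, the adjusted value.

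**Sex term.** A sex main effect adds the same amount at T1, T2 and T3 and cancels from a change. Adding it left the contrasts and their SEs unchanged under all three covariance structures, with sex balanced or unbalanced across arms.

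**Missing data.** With 20% of T3 values removed from the same data set, the MMRM gave −4.561 against −4.222 for completers' raw change. The identity with raw change therefore needs complete data. Results reports no dropout as of March 12, 2026, so it should nearly hold.

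**The case against.** The strongest reply is that nothing here is an error. Hypotheses 2 and 4 are worded as changes from T1, and a group-by-time model with T1 as a response estimates exactly that. It is a standard model, and it is unbiased under randomisation. All of this stands: the point concerns efficiency, on secondary hypotheses.

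Also correct is that the size rests on an unseen r. At r = 0.8 the excess variance is only 11%. Under the plan's own difference and SD, the change contrast for confidence still reaches 80.8% power at r = 0.5.

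A reader might infer more than the documents support:

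- *That leaving out sex causes the loss.* It does not; a sex main effect cancels from the change contrast. The omission is only an inconsistency with the stratification and the ANCOVA.
- *That precision is lost throughout, for confidence and all attitude subscales.* At T3 the baseline-adjusted estimate is already planned. Only T2 lacks one.
- *That participants are wasted or the trial is undersized.* The sample size was set for a t test on hypothesis 1 and is unaffected.
- *That the change contrast is worse than ignoring baseline.* That requires r below 0.5 (with equal SDs), which the documents neither state nor exclude.
- *That differing T3 estimates leave the choice of result open.* The article names hypothesis 1 as the main one, which ranks it above hypothesis 2. Several T3 estimates would still exist after the change, so what is needed is a sentence relating them.

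**Conclusion.** The point holds as a loss of efficiency, not as bias or invalidity. With complete data, equal SDs and linear baseline adjustment, the planned change contrasts carry 2/(1+r) times the variance of a baseline-adjusted analysis: 54%, 33%, 18% and 11% extra for assumed r = 0.3, 0.5, 0.7 and 0.8. The practical consequence is mainly at T2, for the confidence score and the five attitude subscales. At T3 the ANCOVA already gives the efficient estimate. The main hypothesis and the sample size are untouched. The change is worth making because it uses data already being collected, still answers the change hypotheses, and brings the MMRM into line with the ANCOVA in the same section.

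**What to change.** Before any analysis, replace the MMRM specification with one of these:

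1. **Constrained baseline.** Keep T1, T2 and T3 as responses, with time, group-by-T2 and group-by-T3 as fixed effects and no group effect at T1. If sex is added, enter it as sex-by-time, for consistency with the stratification and the ANCOVA.
2. **Baseline as covariate.** Model T2 and T3 only, with T1 score, T1-by-time, group, time, group-by-time and sex. The full analysis set already requires a T1 response, so nobody is lost for want of a baseline.

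In either case, state that the T3 contrast and the hypothesis 1 ANCOVA estimate the same effect, and that the ANCOVA belongs to the main hypothesis.

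The cost is a change of wording, with no new data. Ethical Considerations sends protocol modifications to the ethics board, so review may be needed. Results states that analysis will follow the last assessment, with final data collection expected by December 2026, so the change can be made before any result is seen.

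### Both knowledge scores are compared only by unadjusted rank-sum tests, leaving their T1 values and the stratification factor unused and giving up precision

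*Protocol article*

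**What the plan says.** Hypothesis 5 in the Study Hypotheses section is that "scores for knowledge of sexuality education at T2 and T3 will be higher in the intervention group than in the control group". Hypothesis 6 says the same of the preconception-care score. The first score is a count of correct answers ("Total scores range from 0 to 30"); the second runs from 0 to 5.

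The Statistical Analysis section gives both one method: "For hypotheses 5 and 6, the Wilcoxon rank-sum test will be conducted at time points T2 and T3". It describes them as secondary end points, without multiplicity adjustment. It names no covariate or stratum for them.

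The baseline scores will exist. The Process Assessment section says: "Outcome variables are collected during the baseline assessment (T1), assessment 1 (T2), and assessment 2 (T3", and both knowledge scores are listed as secondary outcomes. Under Random Allocation and Blinding, allocation is stratified by assigned sex at birth and takes place only after the T1 questionnaire is confirmed.

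Other outcomes are handled differently. For hypothesis 1, after a t test, "An analysis of covariance will be conducted with assigned sex at birth and baseline values included as covariates", with a least squares mean difference and its 95% CI. Then: "For hypothesis 3, the same analysis as that for the main hypothesis will be conducted". Hypotheses 2 and 4 use a repeated-measures model with T1 among its time points.

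**The concern.** How much a practitioner knows after the program, or after a waiting period, probably depends in part on what that person knew before. The plan measures prior knowledge on the same instruments and then leaves it out of the comparison. In a trial of 76 participants, sized for 60 evaluable, that makes the comparison noisier than it needs to be. If one arm happens to start with more knowledge, the test cannot correct for it. A real but moderate effect on knowledge could be missed for this reason alone. The attitude outcome, also secondary, does get the adjusted analysis, and no reason is given for treating knowledge differently.

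**Working it through.** **Inputs from the protocol (Sample Size).** Assumed means 18.56 and 23.39, SD 6.5, two-sided 5%, power 80%, 30 evaluable per group, 20% dropout, 76 in total. These concern the primary outcome. No power is stated for the knowledge scores.

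**Reproducing the plan's figure.** Difference 23.39 − 18.56 = 4.83; standardized, 4.83/6.5 = 0.743. The two-sample t calculation gives 29.42, rounded up to 30 per group. With dropout, 30/0.8 = 37.5, rounded up to 38 per group, or 76. The plan's figure reproduces, so 30 per arm is used below.

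**Assumption.** The correlation r between T1 and follow-up knowledge is not in the document; 0.3, 0.5 and 0.7 are taken as a range.

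**Variance.** Adjustment for baseline leaves a fraction 1 − r² of the outcome variance, worth 1/(1 − r²) − 1 in extra participants. The Wilcoxon test has normal-theory efficiency 3/π = 0.955 against the t test. The adjusted analysis would therefore match a 60-participant Wilcoxon test with 60 × 0.955 × (1 − r²) participants. With 30 per arm and 80% power, the detectable effect is 0.736 SD for the t test, 0.736/√0.955 = 0.75 SD for Wilcoxon, and 0.736 × √(1 − r²) adjusted.

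| r (assumed) | Variance left | Equivalent extra participants | Participants to match Wilcoxon at 60 | Detectable effect, adjusted |
|---|---|---|---|---|
| 0.3 | 0.91 | 10% | 52 | 0.70 SD |
| 0.5 | 0.75 | 33% | 43 | 0.64 SD |
| 0.7 | 0.51 | 96% | 29 | 0.53 SD |

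**Simulated power.** 3,000 runs per scenario, 30 per arm, true effect 0.5 SD. Normal scores were rounded and bounded to the scale. Means and SDs were assumed: 18 and 4.5 for the 0-30 score, 2.5 and 1.3 for the 0-5 score.

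| Score | r | Wilcoxon | Analysis of covariance | Rank analysis of covariance |
|---|---|---|---|---|
| 0-30 | 0.3 | 0.454 | 0.505 | 0.487 |
| 0-30 | 0.5 | 0.454 | 0.578 | 0.548 |
| 0-30 | 0.7 | 0.463 | 0.737 | 0.695 |
| 0-5 | 0.3 | 0.440 | 0.482 | 0.480 |
| 0-5 | 0.5 | 0.443 | 0.541 | 0.533 |
| 0-5 | 0.7 | 0.446 | 0.674 | 0.659 |

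With no true effect, the Wilcoxon test rejected in 4.1% to 5.2% of runs, so its type I error is sound. The rank version keeps most of the gain, so the gain does not rest on analysing raw scores. The simulation gave sex no effect on the outcome, so it shows only the gain from baseline.

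**Chance imbalance.** The standardized baseline difference between arms has SD √(2/30) = 0.258. The probability that it exceeds 0.25 SD in either direction is about 33%. A baseline difference of 0.25 SD shifts the expected outcome difference by r × 0.25, or 0.075, 0.125 and 0.175 SD at the three correlations. The planned test leaves that shift in place.

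**The case against.** The strongest reply is that nothing is invalid. Randomization protects the unadjusted rank-sum test, chance imbalance is already part of its null distribution, a rank test is a reasonable choice for bounded discrete scores, and these are secondary end points. All of that stands. It limits the point to efficiency but gives no reason to leave a measured baseline unused.

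Several stronger readings are tempting and are not supported:

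- *That no effect size will be reported.* The article names none for these hypotheses, but a shift estimate or median difference with its CI may be specified in an analysis plan that is not shown.
- *That the test fails the objective because it cannot say how much was gained.* The Objectives section asks whether practitioners gain knowledge, and hypotheses 5 and 6 concern score levels at T2 and T3. A between-group test fits that wording.
- *That only knowledge is treated this way.* The first test named for hypothesis 1 is also unadjusted, and the repeated-measures model for hypotheses 2 and 4 names no sex term. The contrast is with the covariance analysis for hypotheses 1 and 3.
- *That baseline knowledge must vary widely.* Any profession is eligible, but 42 of the 57 enrolled (23 social workers and 19 nurses) come from two groups. Wide variation is plausible, not documented.

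The correlation could also be low. The 30-item test covers a book that the intervention group is sent and asked to read beforehand. High scores in that arm could compress the scale, weaken the correlation and make a common slope doubtful. This is why r = 0.3 is in the range and a robust or bootstrap interval is preferred.

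**Conclusion.** The point holds as a matter of efficiency on two secondary outcomes. The protocol fixes an unadjusted test as the only stated comparison of the knowledge scores, while the baseline values are scheduled for collection and the adjusted method is already used elsewhere in the same section. A reader might infer that the knowledge results would be biased or invalid; the document gives no ground for that.

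The size depends on an unstated correlation. For a 0.5 SD effect with 30 per arm, the loss is about 4 to 5 percentage points of power at r = 0.3, 10 to 12 at 0.5, and 23 to 27 at 0.7. It is small at the low end and substantial at the high end. The figures assume roughly normal underlying scores and a common slope. The change is worth making because it costs little, but the trial's main conclusion does not depend on it.

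**What to change.** Before any outcome analysis, prespecify for hypotheses 5 and 6 a comparison at T2 and at T3 adjusted for the T1 score and assigned sex at birth:

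- **0-30 score:** analysis of covariance, reporting the adjusted mean difference with a robust or bootstrap 95% CI.
- **0-5 score:** rank analysis of covariance. A proportional-odds model is an alternative only if cell counts allow, since 60 participants over six possible values average 10 per value. Report its odds ratio and CI if it is used.
- **Both:** keep the Wilcoxon rank-sum tests as sensitivity analyses.

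The cost is analysis-plan wording, with no new data and no change to trial conduct. The T1 scores are already scheduled: allocation follows the T1 questionnaire, and the full analysis set excludes anyone without a T1 response. Collection is not finished (57 enrolled and 46 with a final assessment on March 12, 2026; last data expected by December 2026) and analysis has not been done, so the change can still be prespecified. The downside is a mild model assumption, which the retained Wilcoxon tests check.
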